### 4.4. Cost-Effectiveness Analysis

We will perform the cost-effectiveness analysis (CEA) by measuring the costs and benefits in the yoga program group and the strengthening exercise program group. Mean differences in total costs and benefits between the yoga program and strengthening exercise program at 12 weeks will be calculated. Incremental cost-effectiveness ratios (ICERs) will be determined by dividing the difference in total costs by the difference in total benefits (assessed as QALY) for both groups (equation below). We will also conduct a subgroup analysis based on the degree of knee pain at baseline, adherence to the yoga program, sex, and socioeconomic status.

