## Abstract

Osteoarthritis (OA) is a common joint disorder for which there is no cure. Current treatments are suboptimal. Exercise is a core treatment for knee OA, with muscle strengthening exercise commonly recommended. Yoga is a mind-body exercise intervention that can improve flexibility, muscle strength, balance, and fitness and potentially reduce symptoms of OA. However, there is a scarcity of robust, high-quality conclusive evidence on the efficacy of yoga in knee OA. We are currently conducting the first randomised comparative effectiveness and cost-effectiveness trial of a yoga program compared with a strengthening exercise program in patients with symptomatic knee OA. This study protocol describes the design and conduct of this trial. The YOGA study is a phase III, single-centre, parallel, superiority, randomised, active-controlled trial which will be conducted in Hobart, Australia. One hundred and twenty-six participants (63 in each arm) aged over 40 years with symptomatic knee OA will be recruited from the community and randomly allocated to receive either a 24-week yoga program (3×/week) or a strengthening exercise program (3×/week). The primary outcome will be change in knee pain over 12 weeks, assessed using a 100 mm visual analogue scale (VAS). The secondary outcomes include change in knee pain, patient global assessment, physical function, quality of life, gait speed, biomarkers, and others over 12 and 24 weeks. We will also assess whether the presence of neuropathic pain moderates the effects of yoga compared to strengthening exercise. Additional data, such as cost and resource utilization, will be collected for the cost-effectiveness analysis. The primary analysis will be conducted using an intention-to-treat approach. Adverse events will be monitored throughout the study. Once completed, this trial will contribute to the knowledge of whether yoga can be used as a simple, effective, low-cost option for the management of knee OA, thus saving economic costs in the healthcare system.

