### 3.5. Randomisation and Blinding:

Allocation of participants in a 1:1 ratio to either the yoga program or strengthening exercise program will be based on computer-generated random numbers prepared by a statistician with no involvement in the trial. The administering institute will maintain the code-break for the full randomisation schedule. Allocation concealment and blinding will be ensured by having two research nurses coordinate the trial. Clinical assessments will be taken by the research nurse blinded to the group allocation. Due to the nature of the intervention, participants will not be blinded to the treatment allocation. Thus, patient-reported outcomes will not be blinded.

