4.Self-reported adherence to the yoga or strengthening exercise program from baseline to 12 and baseline to 24 weeks will be assessed using an online logbook and defined as the percentage of prescribed sessions undertaken;5.Change in body fat will be assessed using bioelectrical impedance analysis (BIA) (BIA analyser, Quantum II, RJL Systems, MI, USA) at baseline, week 12, and week 24. We will assess fat-free mass, percentage of fat-free mass, fat mass, and percentage of fat mass;6.The OARSI-OMERACT responder criteria: This will be employed to generate a responder categorical variable (0 = non-responder, 1 = responder) based on improvement in WOMAC pain, function, and patient’s global assessment;7.Pain medication use: There will be no constraints with regard to the use of analgesic medications. All participants will be allowed to continue taking the medications they are taking at their screening visit for the duration of the trial. Participants will be asked to keep medications as stable as possible, but if a participant requires an increase in analgesics, this will be permitted, and the reason for the dose increase and the dose used will be documented. Any medication changes will be documented with the reason, drug name, and dose. Medication change will be classified as commenced or increased, discontinued, or decreased, or stable use or non-use, and the change in total number of pain medications. A rescue medication, paracetamol, will be provided if the participant requests it. Medication use will be recorded at baseline and during each follow-up period.

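### Adherence to yoga, a post-randomisation variable with no counterpart in the strengthening arm, is listed as a subgroup for the between-arm cost-effectiveness ratio, so that result is non-randomised and open to selection bias

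*Protocol article*

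**What the plan says.** Section 4.4 defines the cost-effectiveness result as a contrast between arms: "Mean differences in total costs and benefits between the yoga program and strengthening exercise program at 12 weeks will be calculated". The incremental ratio (ICER) is obtained by "dividing the difference in total costs by the difference in total benefits (assessed as QALY) for both groups". The same section then adds a "subgroup analysis based on the degree of knee pain at baseline, adherence to the yoga program, sex, and socioeconomic status". It names no method for the adherence part and does not mark it as exploratory or non-randomised.

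Adherence is defined in section 3.9, item 4. The outcome is "Self-reported adherence to the yoga or strengthening exercise program from baseline to 12 and baseline to 24 weeks", taken from an online logbook and "defined as the percentage of prescribed sessions undertaken".

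Section 3.5 states that "participants will not be blinded to the treatment allocation". The Abstract says "The primary analysis will be conducted using an intention-to-treat approach". That sentence covers the primary analysis and does not reach this economic subgroup.

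**The concern.** A subgroup estimate of a treatment contrast keeps the protection of randomisation only if the subgroup could have been formed at baseline, in the same way in both arms. Baseline pain, sex and socioeconomic status meet that condition. Adherence does not. It builds up after allocation, over the same 12 weeks as the costs and QALYs, and it may depend on how the participant is faring. People whose knees improve may attend more. Equally, people who improve may stop coming and those with persistent pain may keep attending. Both adherence and the utility questionnaires are self-reported by participants who know their allocation, so their errors may also be related.

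At stake is the reading of one secondary result. Section 4 states the hypothesis that yoga is the more cost-effective program. A ratio for yoga adherers, listed with ordinary subgroups and without a caveat, could be read as randomised evidence for or against that hypothesis.

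**Working it through.** The plan states no figure for this analysis, so the check is mainly one of reading, followed by an illustration.

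**1. When each subgroup variable is fixed**

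| Variable (section 4.4) | Fixed before allocation? | Defined alike in both arms? |
|---|---|---|
| Knee pain at baseline | Yes | Yes |
| Sex | Yes | Yes |
| Socioeconomic status | Yes, if recorded at baseline | Yes |
| Adherence to yoga | No: sessions undertaken in follow-up (section 3.9) | No: strengthening participants are not prescribed yoga |

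**2. Between-arm comparisons open to the analyst**

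- *Yoga adherers against all controls.* A selected part of one arm is set against the whole of the other.
- *Adherers against adherers, each to their own program.* Section 3.9 makes this possible, since one definition serves both arms. But those who persist with yoga need not resemble those who persist with strengthening, so randomisation does not balance the two groups.

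Neither is a randomised comparison. A within-arm description would be legitimate, but it gives no yoga-versus-strengthening ratio.

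**3. Illustration of how large selection could be**

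The inputs here are assumptions, not taken from the documents: no true treatment effect; a latent normal adherence score with correlation r to the outcome; a share p of the yoga arm classed as adherent. With c = z(1 − p) and φ the standard normal density:

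- adherers minus all controls = r × φ(c) / p SD
- non-adherers minus all controls = −r × φ(c) / (1 − p) SD

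| p | r | Adherers (SD) | Non-adherers (SD) |
|---|---|---|---|
| 0.5 | 0.1 | +0.08 | −0.08 |
| 0.5 | 0.3 | +0.24 | −0.24 |
| 0.5 | 0.5 | +0.40 | −0.40 |
| 0.7 | 0.3 | +0.15 | −0.35 |
| 0.8 | 0.1 | +0.04 | −0.14 |
| 0.8 | 0.5 | +0.18 | −0.70 |

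For p from 0.5 to 0.8 and r from 0.1 to 0.5, the spurious difference is 0.04 to 0.40 SD for adherers and −0.08 to −0.70 SD for non-adherers. With negative r every sign reverses. With r = 0 the difference vanishes.

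**4. Splitting both arms**

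In the same model the shift is the yoga value minus the strengthening value. It cancels only if the two match. For example, with r = 0.3 in both arms, 50% adherent to yoga (0.239) and 80% adherent to strengthening (0.105), the shift is 0.239 − 0.105 = 0.134 SD.

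**5. On the QALY scale**

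Assume further a utility SD of 0.2 and a median split (p = 0.5).

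- Gap constant over 12 weeks: 0.080 × 0.2 × 12/52 = 0.0037 QALY at r = 0.1, and 0.239 × 0.2 × 12/52 = 0.0110 at r = 0.3.
- Gap growing linearly from zero at baseline: half of that, about 0.002 to 0.0055 QALY. This is how an area-under-the-curve calculation from the week 0 and week 12 measurements in Table 1 would treat it.

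The cost numerator of the ratio would come from the same selected participants and could shift too. Nothing in the documents allows that to be quantified.

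**The case against.** The strongest reply is that section 4.4 gives a single clause in a condensed article. It does not say that adherers will be set against all controls, and it does not rule out a complier-average analysis or a within-arm description. Such detail commonly belongs in the analysis plan, which is not shown. This stands as far as the choice of method goes. It does not excuse listing a follow-up variable among baseline subgroups of a between-arm ratio, because no later detail can make adherence a baseline characteristic. The authors do label a related analysis when they want to: section 4.3 calls the neuropathic-pain moderator analysis exploratory.

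A second reply is that section 4.4.2 plans change-from-baseline and regression approaches to QALYs. These may reduce differences in starting utility. They do not remove selection on improvement during treatment.

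Three stronger readings are tempting, and the documents do not support them.

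- *That adherence exists in one arm only.* This is true of the variable named in section 4.4. Section 3.9 records adherence in both arms, each to its own program.
- *That the subgroup result is biased in favour of yoga.* No passage gives a link between adherence and outcome. It could run either way, and the cost side is unknown.
- *That the bias would be as large as a plausible between-arm QALY difference.* The documents give no such difference. A full 12 weeks at utility 1.0 is 12/52 = 0.23 QALY. That is a ceiling, of which 0.0037 to 0.0110 is 1.6% to 4.8%, and it says nothing about what difference is plausible.

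**Conclusion.** The point holds in limited form. As listed, the adherence subgroup would give a yoga-versus-strengthening ratio that is not a randomised comparison and is open to selection bias. The bias is absent only if adherence is unrelated to prognosis for costs and QALYs or, when both arms are split, if selection happens to act alike in each. The SD and QALY figures rest wholly on assumed inputs. They show that modest correlations are enough to move the estimate, and they do not predict what this trial will find.

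The reach is narrow: one of four variables in a subgroup analysis of a secondary economic outcome. The primary pain analysis, the overall cost-effectiveness ratio and the other three subgroups are unaffected. It is still worth correcting before analysis, because the change is small.

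**What to change.** In section 4.4, delete adherence to the yoga program from the subgroup list and keep baseline pain, sex and socioeconomic status, with socioeconomic status taken from baseline data.

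If the effect under good adherence is of interest, describe it as a separate analysis, labelled exploratory and non-randomised:

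- use the section 3.9 definition (percentage of prescribed sessions) in both arms, with any cut-off fixed before the data are seen;
- name the causal method and state its assumptions. A principal-stratum or complier-average analysis has to say how stratum membership is identified, since nobody's adherence to the other arm's program is observed. Inverse-probability weighting has to assume that the recorded covariates capture what drives both adherence and outcome;
- report it apart from the baseline subgroups.

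The adherence data are already to be collected, so no new measurement is needed. The cost is the loss of one secondary subgroup result or, if the separate analysis is kept, a little extra analysis work.

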#### 4.4.1. Measurement of Costs

The health questionnaires completed by participants at baseline and 12 weeks will provide data on “health service use”. These data will include visits to GPs, practice nurses, and any other health professionals (e.g., physiotherapists) for the treatment and/or management of knee OA. To estimate total costs, we will assign unit costs for each visit to a health care professional. Unit costs will be obtained from national published sources such as the appropriate Australian Annual Medicare Statistics providing health service unit cost and the Indexation of Medicare Benefits Schedule [49].

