## 4. Health Economics Outcomes (Secondary Outcomes):

Health-related quality of life (HRQoL) and health state utility (HSU) will be assessed using the Assessment of Quality of Life (AQoL-8D) and the EuroQol 5 dimensions (EQ-5D-5L) instruments. In combination with the clinical data, these data will be used to conduct a cost-effectiveness analysis of the yoga program versus the strengthening exercise program [44,45]. We will test the hypothesis that the yoga program will be more cost-effective than the strengthening exercise program.

The health economic outcomes to be collected as the secondary outcome will include:8.Change in concomitant medications (assessed using self-reported medication history questionnaire) from baseline to 12 and baseline to 24 weeks and associated costs;9.Change in QoL (assessed by AQoL-8D and EQ-5D-5L) from baseline to week 12 and baseline to 24 weeks [46,47,48];10.Change in health resource utilisation (assessed using a self-reported questionnaire) at 12 weeks.

Additional details on these measures are provided in Table 1 and the section describing cost-effectiveness analysis.

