### 4.2. Sample Size Calculation

Our power calculations are based on a sample size that can document the superiority of yoga compared to strengthening exercise by an amount that meets the minimal clinically important difference (MCID). Based on the MCID of 15 mm in VAS pain (a numerical scale ranging from 0 (no problem) to 100 (maximum problem)), the two-sided significance level of 0.05, 90% power, and SD of VAS pain change 22.5, we will need a total of 98 participants. Assuming a scenario of around 20% dropout, we will need 126 participants.

The above sample size will allow us to detect a non-inferiority of yoga with strengthening exercise. Non-inferiority would be declared if the mean change in knee pain (assessed using VAS) in the yoga group was not significantly worse than the mean change in the strengthening exercise group, within a pre-stated margin of non-inferiority (∆), in this case, set at 10 mm. Overall, 126 participants will give us 80% power to detect the non-inferiority of yoga compared with strengthening exercise.

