### 4.3. Statistical Analyses

The comparisons of pain and other continuous outcomes will be done employing a repeated-measures mixed model incorporating terms of treatment, time, and respective baseline values as covariates. The treatment effect will be calculated by the intervention by time interaction followed by the main effects model with only group and time. We will also assess the effects of potential confounders or interaction with treatment by covariates, including age, sex, BMI, disease severity, comorbidities, health status, and use of pain medications. A two-sided *p*-value less than 0.05 will be considered to indicate the statistical significance, and the results will be shown as the between-group differences with 95% confidence intervals (95% CIs) of the differences.

We will explore the role of clustering effects in the trial by performing a sensitivity analysis examining the implications of clustering by the instructor by adding an instructor random effect to our mixed-effects model.

We will also perform an exploratory analysis to investigate whether the presence or absence of neuropathic pain, as assessed by the painDETECT questionnaire, is a potential moderator that influences response to treatment for the primary outcome at 12 weeks. To assess the moderation of the effect by painDETECT (binary moderator), an interaction term between the randomised group and the potential moderator will be included in outcome regression models.

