#### 4.4.2. Measurement of Benefit

As described under secondary outcomes, AQoL-8D and EQ-5D-5L will be used to determine HSU for each participant. Mean scores and measures of dispersion will be calculated for both groups. Quality-adjusted life-years (QALYs) will be calculated using two approaches: change from baseline (CfB) and area under the curve (AUC) approach with/without linear regression [44,45].

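### The ICER's cost difference is a raw difference in means although baseline service use is collected, and Section 4.4.1 gives no costing window: a cheap gain in precision is available

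*Protocol article*

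**What the plan says.** Section 4.4.1 draws on two questionnaires: "The health questionnaires completed by participants at baseline and 12 weeks will provide data on" health service use. It continues: "To estimate total costs, we will assign unit costs for each visit to a health care professional". No period is attached to the visits that are priced.

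Section 4.4 states the comparison: "Mean differences in total costs and benefits between the yoga program and strengthening exercise program at 12 weeks will be calculated". The formula printed in Section 4.4.3 has the difference between the two arms' mean costs as its numerator, with no adjustment.

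Section 4 lists the related secondary outcome as "Change in health resource utilisation (assessed using a self-reported questionnaire) at 12 weeks".

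Table 1 schedules the health economics items at week 0 and week 12, with randomisation also at week 0.

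Baseline values are used elsewhere. The Section 4.3 model for pain and the other continuous outcomes is described as "incorporating terms of treatment, time, and respective baseline values as covariates". For QALYs, Section 4.4.2 names "change from baseline (CfB) and area under the curve (AUC) approach with/without linear regression". Neither provision is repeated for costs.

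**The concern.** The baseline questionnaire describes service use before either program starts, so the intervention cannot affect it. Its natural use in a cost comparison is as a covariate. People who use many services before randomisation tend to use many afterwards, and adjusting for this removes noise from the difference between arms. The article provides for regression on the benefit side of the ICER and for baseline covariates in the clinical models, but gives the cost side a plain difference in means.

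The lack of a costing window in Section 4.4.1 adds a smaller problem. A reader cannot tell from that section alone whether baseline visits are a reference value, are left out of the cost total, or form part of it.

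The cost difference is the ICER numerator and one of the two quantities behind the CEAC. Section 4 also states a hypothesis that yoga will be the more cost-effective program. Precision matters here, since the trial is sized for pain and not for costs.

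**Working it through.** **Figures in the plan.** There is no cost figure to reproduce: the article gives no cost mean, SD, recall period or baseline to follow-up correlation. The check therefore compares estimators on a relative scale.

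**Assumed inputs.** r is the correlation between a participant's baseline cost and follow-up cost, taken as 0.3, 0.5 and 0.7, with 0 as the limiting case. Follow-up cost has variance s². Where the two periods are added or subtracted, baseline cost is also given variance s². That equality is a further assumption and depends on the unstated recall period.

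**Per-participant variance behind the cost difference**

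- Follow-up costs only, unadjusted: s²
- Follow-up costs adjusted for baseline cost: (1 − r²)s². This needs r but not equal variances.
- Change from baseline: 2(1 − r)s²
- Baseline plus follow-up: 2(1 + r)s²

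**Standard errors, with follow-up only set to 1**

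| r | Adjusted, √(1 − r²) | Reduction in SE | Change score, √(2(1 − r)) | Both periods summed, √(2(1 + r)) |
|---|---|---|---|---|
| 0 | 1.00 | 0% | 1.41 | 1.41 |
| 0.3 | √0.91 = 0.95 | 5% | √1.4 = 1.18 | √2.6 = 1.61 |
| 0.5 | √0.75 = 0.87 | 13% | √1.0 = 1.00 | √3.0 = 1.73 |
| 0.7 | √0.51 = 0.71 | 29% | √0.6 = 0.77 | √3.4 = 1.84 |

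In sample-size terms, adjustment is worth a factor of 1/(1 − r²): 1/0.91 = 1.10, 1/0.75 = 1.33 and 1/0.51 = 1.96.

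The change score does not replace adjustment. Its SE is 1.24, 1.15 and 1.08 times the adjusted SE at r = 0.3, 0.5 and 0.7.

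**Simulation with skewed costs.** Gamma-distributed costs, 63 per arm as planned, 20,000 trials, no true difference between arms:

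- r = 0.3: SE 0.1250 follow-up only, 0.1194 adjusted (ratio 0.96), 0.2008 summed (ratio 1.61)
- r = 0.5: SE 0.1264 follow-up only, 0.1079 adjusted (ratio 0.85), 0.2194 summed (ratio 1.74)
- r = 0.7: SE 0.1261 follow-up only, 0.0890 adjusted (ratio 0.71), 0.2328 summed (ratio 1.85)

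The formulas hold up under skewness. The mean of the summed difference stayed within 0.0012 of zero at these correlations, so even that estimator loses precision without systematic bias.

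**The case against.** A reader might infer from Section 4.4.1 that pre-randomisation visits are added into total costs, since both questionnaires are named and each visit is priced. The article does not say this. The section gives the source of the visit data and the way a visit is valued; it contains no statement that the two periods are summed. Section 4.4 dates the cost contrast at 12 weeks, and Section 4 treats service use as a change, which makes baseline a reference and not an addend. The 1.61 to 1.84 ratios in the last column of the table belong to that disfavoured reading and do not measure the defect.

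Three further objections deserve weight.

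- A difference in means between randomised arms is valid and unbiased. This stands: the point is about efficiency.
- A journal article commonly leaves the costing window to the full protocol or an economic analysis plan, neither of which is shown. This largely stands, and on its own the missing window would be only a request for clarification.
- Section 4.3 applies baseline covariates to continuous outcomes, and change in resource use is listed among the secondary outcomes, so an adjusted analysis of that outcome is arguably already planned. This stands for the listed outcome but does not reach the ICER: Sections 4.4 and 4.4.3 define its numerator from plain means. The sensitivity analyses promised in Section 4.4.3 are not specified, and the regression in Section 4.4.2 concerns QALYs.

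What remains is a stated estimator that can be improved with data already scheduled for collection.

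**Conclusion.** The point holds as a minor, nearly free improvement. The article fixes the ICER numerator as an unadjusted difference in mean costs and gives baseline service use no stated role in it. With follow-up visits only, adjusting for baseline cost would reduce the SE of the cost difference by about 5% to 29% for r between 0.3 and 0.7, and would gain nothing at r = 0. These sizes rest on an assumed correlation that the article neither gives nor implies.

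No error in the comparison of arms is shown, and no systematic bias arises under any of the readings. The open costing window calls for one clarifying sentence; it is not evidence that pre-randomisation visits are counted as costs.

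**What to change.** In Section 4.4.1, state that total costs cover the period from randomisation to week 12 only, and that baseline service use is costed with the same unit costs for use as a covariate.

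In Section 4.4, estimate the cost difference by regressing post-randomisation cost on arm and baseline cost. Keep costs on their original scale so that the arm coefficient is still a difference in mean costs. Use that adjusted difference in the ICER and CEAC, and report the raw difference as a sensitivity analysis. Fix this before the costs are analysed, so that the choice of estimator cannot depend on the results.

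The cost is two or three sentences and one extra regression. No new data are needed.

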## Figures and Tables

**Figure 1 jfmk-07-00084-f001:**
[figure not shown]
Trial design.

**Table 1 jfmk-07-00084-t001:** SPIRIT (Standard Protocol Items: Recommendations for Interventional Trials) diagram of enrolment, interventions, and assessments for the YOGA trial.

Items/Variables	Screening	Baseline (week 0)	Week 4	Week 8	Week 12	Week 16	Week 20	Week 24
Informed consent	x							
Randomisation		x						
Safety for exercise clearance	x							
ACR clinical criteria for knee OA	x							
Medicare number		x						
Clinical measures								
Blood (stored for cartilage/synovium/ inflammatory markers)		x			x			x
Core physical function tests		x			x			x
Leg muscle strength test		x			x			x
Height and weight		x			x			x
Gait characteristics		x			x			x
Body composition (using BIA)		x			x			x
Physical activity (using accelerometers)		x						x
Questionnaires								
Knee pain VAS	x	x	x	x	x	x	x	x
Knee WOMAC		x	x	x	x	x	x	x
PainDETECT		x			x			x
PHQ-9		x			x			x
Patient global evaluation		x	x	x	x	x	x	x
Pain medication use/change in use		x	x	x	x	x	x	x
Health Economics Outcomes: Medication cost diary Health service utilisation (visit to GP, practice nurses, and any other health professionals (e.g., physiotherapists)) Employment/days off work Concession/health care card Private health insurance Transport and specialised equipment costs		x			x			
Safety (AEs)			x	x	x	x	x	x
EQ-5D and AQoL-8D		x			x			x
Consent to contact for future studies								x
Early withdrawal information		As required						

ACR, American College of Rheumatology; AE, adverse events; AQoL-8D, Assessment of Quality of Life-8 dimension; BIA, Bio-Electrical Impedance Analysis; EQ-5D, European Quality of Life Five Dimension; GP, general practitioner; OA; osteoarthritis; PHQ-9, Patient Health Questionnaire-9; VAS, visual analogue scale; WOMAC, Western Ontario and McMaster Universities Osteoarthritis Index.

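### The costing rule in section 4.4.1 prices health professional visits only, omitting program delivery and the other cost data collected, so the ICER may miss a material cost difference

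*Protocol article*

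**What the plan says.** Section 4.4.1 describes the resource data and the pricing. On timing: "The health questionnaires completed by participants at baseline and 12 weeks will provide data on" health service use. On content: "These data will include visits to GPs, practice nurses, and any other health professionals (e.g., physiotherapists) for the treatment and/or management of knee OA". On how these become a total: "To estimate total costs, we will assign unit costs for each visit to a health care professional". On prices: "Unit costs will be obtained from national published sources such as the appropriate Australian Annual Medicare Statistics providing health service unit cost", together with the indexation of the Medicare Benefits Schedule.

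Section 4.4 fixes the comparison: "Mean differences in total costs and benefits between the yoga program and strengthening exercise program at 12 weeks will be calculated". The equation in section 4.4.3 divides the difference in mean group cost by the difference in mean group QALY. Section 4 says the trial will test whether yoga is the more cost-effective program.

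Other cost data appear elsewhere. Section 4, item 8, covers change in concomitant medication "from baseline to 12 and baseline to 24 weeks and associated costs". Item 10 is "Change in health resource utilisation (assessed using a self-reported questionnaire) at 12 weeks". The health economics row of Table 1 opens with "Health Economics Outcomes: Medication cost diary" and goes on to service use, employment and days off work, concession card, private insurance, and travel and equipment outlays. The row is marked at baseline and week 12.

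Section 3.6 gives the delivery details. Both arms have two one-hour led sessions a week for 12 weeks in groups of about 10, then home practice supported by emails and videos. Yoga teachers deliver the yoga arm; physiotherapists or exercise physiologists deliver the strengthening arm.

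**The concern.** An ICER that compares two programs needs the cost of providing them. The rule in section 4.4.1 produces the cost of other care that participants use while enrolled. That is a downstream consequence of the programs, not their price. Instructor time, instructor training, venue, equipment and digital content have no place in the rule and no row in Table 1.

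Three things follow.

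- The economic hypothesis, and the description of yoga in the abstract and discussion as a possibly low-cost option, would rest on a cost total that leaves out both programs.
- Data collected from participants on medication, lost work, travel and equipment have no stated route into the total, and no perspective is named that would settle which of them belong.
- The rule could treat the arms unequally. It counts visits to physiotherapists and other health professionals for knee OA. A participant in the strengthening arm could report trial classes as such visits, whereas classes led by yoga teachers would probably not qualify. Nothing in section 4.4.1 prevents this.

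**Working it through.** The documents give no price, cost, utility difference or ICER, so there is no figure to reproduce. The check has two parts.

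**Where each cost item stands in the text**

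| Item | Collected or mentioned | In the section 4.4.1 rule |
|---|---|---|
| Health professional visits | 4.4.1; section 4 item 10; Table 1, baseline and week 12 | Yes |
| Medication cost | Section 4 item 8, to weeks 12 and 24; Table 1 cost diary, baseline and week 12 | No |
| Days off work | Table 1, baseline and week 12 | No |
| Travel and equipment | Table 1, baseline and week 12 | No |
| Program delivery (instructors, venue, digital support) | Delivery described in 3.6, no cost anywhere | No |

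The medication rows also disagree on timing: item 8 promises costs to week 24, while the cost diary in Table 1 stops at week 12.

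**How large an omitted delivery difference could be**

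Inputs from section 3.6: 2 led hours per week × 12 weeks = 24 led hours, in groups of about 10, the same in both arms.

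Assumed inputs, not in the documents: an hourly instructor cost difference between arms of AUD 0, 20, 50 or 100; a utility difference of 0.01, 0.02 or 0.05 at week 12, starting from zero at baseline and growing linearly.

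Delivery cost difference per participant = 24 × hourly difference ÷ 10:
- 24 × 0 ÷ 10 = AUD 0
- 24 × 20 ÷ 10 = AUD 48
- 24 × 50 ÷ 10 = AUD 120
- 24 × 100 ÷ 10 = AUD 240

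QALY difference over 12 weeks = 0.5 × (12/52) × utility difference:
- 0.5 × (12/52) × 0.01 = 0.00115
- 0.5 × (12/52) × 0.02 = 0.00231
- 0.5 × (12/52) × 0.05 = 0.00577

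Shift in the ICER = cost difference ÷ QALY difference, in AUD per QALY:

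| Cost difference per participant | Utility 0.01 | Utility 0.02 | Utility 0.05 |
|---|---|---|---|
| AUD 0 | 0 | 0 | 0 |
| AUD 48 | 41,600 | 20,800 | 8,320 |
| AUD 120 | 104,000 | 52,000 | 20,800 |
| AUD 240 | 208,000 | 104,000 | 41,600 |

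If the full utility difference were present throughout the 12 weeks, the QALY difference would double and each shift would halve. The direction of the shift depends on which arm costs more to deliver, which the documents do not say.

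**The case against.** The strongest reply is that this is a condensed article and the full protocol or a health economics plan may price delivery. Delivery cost would come from the trial's own accounts, so it would not be expected in a participant questionnaire or in an assessment schedule. The ICER equation uses mean group cost, which does not exclude delivery, and the unit-cost sources are introduced as examples. This has some force against reading anything into Table 1. It does not dispose of the point, because section 4.4.1 is not silent: it states how total costs are formed, and that rule covers visits.

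Three stronger readings are tempting, and the documents do not support them.

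- A reader might infer that delivery is the main cost difference between the arms. Led hours and approximate group size are matched, only the increment enters the ICER, and no prices are given. The increment could be zero.
- A reader might infer that the trial collects visit data only. It does not: section 4 and Table 1 list medication, work-loss, travel and equipment data. The gap is in the rule that should use them.
- A reader might infer that stopping at 12 weeks of a 24-week program is an error, since utilities are also measured at week 24. The 12-week comparison is a stated choice, consistent for resource use across sections 4 (item 10), 4.4 and 4.4.1 and Table 1. It matches the primary endpoint and the led phase. It drops service use and QALYs in weeks 13-24 but no led-session cost. A 24-week base case would need a further questionnaire in a trial already running, so it is a trade-off and not a correction.

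The medication timing conflict is also limited. Section 3.9 records medication use during each follow-up period, and Table 1 schedules pain medication use to week 24. Costs for pain medicines to week 24 could therefore be derived; only the cost diary ends at week 12.

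**Conclusion.** The point holds in this form. As written, the rule leaves the cost of both programs out of the ICER, together with other cost data the trial sets out to collect. Because different staff deliver the two arms, it may miss a material incremental cost, and it may count trial classes in one arm and not the other. The ICER so defined is not a proper test of the cost-effectiveness hypothesis.

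The documents do not allow the size to be stated. Under the assumed non-zero inputs the shift runs from about AUD 8,300 to AUD 208,000 per QALY, and it is zero if delivery costs are equal. What the range shows is sensitivity: a 12-week QALY difference is so small that even a modest cost per participant can change the conclusion. The cost-effectiveness analysis is secondary, and the clinical primary analysis is untouched. The change should still be made, because cost-effectiveness is one of the trial's stated aims.

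**What to change.** Rewrite the rule in section 4.4.1 as follows, before the cost data are analysed.

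1. Name the perspective of the analysis.
2. Define total cost per arm as program delivery cost (instructor hours divided by class size, venue, equipment, digital support) plus health service use, medication, and the other Table 1 cost items that fall under that perspective. State how each item is priced.
3. Count trial classes in the same way in both arms, under delivery cost, and state that they are not also counted as health professional visits.
4. Reconcile the medication cost timing in section 4, item 8 (weeks 12 and 24) with the cost diary in Table 1 (baseline and week 12).
5. Keep 12 weeks as the base-case horizon.

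The cost is small. Delivery costs come from the trial's own records, and the other items are already scheduled for collection, so no new visit or questionnaire is required. If trial classes may already have been reported as visits, those entries need to be identified and removed during data cleaning.
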